#### Duration of Data Access

The University of Manchester will request primary care data on study participants for the period April 1, 2016, to March 30, 2022, through DMW This will enable a 3-year assessment of *baseline* levels of risk factors such as HbA_1c_ and blood pressure before study commencement (July 2019), and up to the end of the intervention (March 31, 2022).

### Clinical and Biochemical Data From NHS Digital in Participants and in Controls not Providing Consent

Our study involves comparing intervention-related changes in risk factors, such as HbA_1c_ levels, in study participants with the changes occurring in a control patient cohort not receiving the intervention.

NHS Digital will use their General Practice Extraction Service (GPES) to provide GP data on all patients with T2D across GM (approximately 160,000 people) between April 1, 2016, to March 31, 2022. The core data items will include age, sex, ethnicity, GP postcode (to assess socioeconomic deprivation), diabetes type and duration, blood pressure, cholesterol, creatinine, eGFR, smoking and body weight, height, BMI, medication, diabetes clinic attendance in primary care, and hospital visits including emergency visits.

To distinguish between DMW participants and nonparticipants in the GPES data, the following steps will be taken:

DMW will supply NHS Digital with details of DMW participants including NHS numbers, GP practice with which the participant is registered, DMW generated study ID, and whether the participant is using Oviva, Changing Health, or MyCognition.NHS Digital will use NHS numbers of participants to create a DMW participant flag within the GPES data for GM. NHS numbers will then be removed.NHS Digital will supply the University of Manchester with GPES data for patients from GM with T2D.University of Manchester will store and analyze these data in accordance with NHS Digital requirements and Data Sharing Agreement.

Our study design requires that control participants be matched to participants receiving the intervention on age, sex, ethnicity, and socioeconomic deprivation (defined by GP postcode). Therefore, we require information on these 4 characteristics, in addition to the clinical and biochemical data. Socioeconomic deprivation level will be assessed from the GP postcode to minimize the risk of patients being identified. The University of Manchester will not receive any information that will enable DMW participants or control participants to be identified.

### Analysis

#### Overview

First, the generalizability and relevance of the intervention in the context of GM will be assessed. We will descriptively compare participants in the interventions to other populations: those who did not participate, the population of GM, and the population of England. For the comparison to those who did not take up the intervention, we will use data on age, sex, ethnicity, residence location socioeconomic deprivation quintile (2019 Index of Multiple Deprivation) and risk factors (from their electronic record) for a comparison with the participants. For the GM and England comparisons, we will compare patients based on age, sex, risk factors, and comorbidities using data sourced from NHS Digital.

Second, we will examine engagement with the intervention (as quantified by relevant metrics in the app, eg, visits and time spent), and descriptively assess how it varies across age groups, sex, ethnic groups (South Asian, Black, mixed, White, and other populations) and socioeconomic deprivation quintiles. A multiple linear regression model will be used to more formally evaluate the association between the variables listed above (age, sex, ethnicity, and socioeconomic deprivation) and engagement.

Third, we will aim to use quasi-experimental methods to evaluate the effectiveness of the intervention on each outcome by comparing prospective changes in outcomes between matched participants and controls and by performing pre- versus postintervention comparisons in participants only. Matching will be performed using the caliper method, which is a modification of the nearest neighbor matching procedure that imposes a tolerance on the difference in cohort characteristics [37]. Here, we will combine calipers relating to age range (+2 or −2 years) and with exact match of gender, ethnicity, and general practice. In the matched group approach, participants receiving the interventions will be randomly matched to nonparticipants on age, sex, ethnicity, and general practice (as a proxy for socioeconomic deprivation).

Where there are differences between participants and controls in relation to matched characteristics or other characteristics such as prevalent cardiovascular disease, we will include these variables as covariates regression models.

In the presence of time series data, we will use an interrupted time series design for each outcome of interest, which takes into account the preintervention trends of the outcome as well as the information on controls and quantify the effect of the intervention on future outcome levels. If only 2 time points are available (eg, before and after the intervention), we will use a simple linear regression model with clustered errors or a paired 2-tailed *t* test to compare means in each outcome at the 2 time points.

For example, for the main outcome, change in HbA_1c_ levels, we will compare changes from baseline (defined as April 1, 2016, to July 1, 2019) during the intervention period (July 1, 2019, to March 31, 2022) in matched participants and controls after adjusting for clinically significant differences in baseline weight, blood pressure, cholesterol, creatinine, cardiovascular disease, and smoking.

If the numbers of cases and controls are large, we will explore effect heterogeneity in subgroup analyses (as separate models or using interaction terms in the main models described above) by ethnicity, age groups, socioeconomic deprivation quintile, cognitive function (assessed by MyCognition), and level of engagement with digital interventions.

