#### Participants and Recruitment

We will take a census approach to recruitment in that all eligible participants in GM will be invited to participate. Identification of potential participants will take place primarily through searches of primary care practice databases to identify patients with T2D. Practice searches will be facilitated by the staff of the Greater Manchester Diabetes Clinical Research Network whenever possible. Letters from the practice, in most cases, will make initial contact with potential study participants. In some cases (according to practice preference), a text message from the practice to the patient or an email sent from the practice to the patient will be used. Posters advertising the study will be made available in practice clinics and waiting rooms.

We expect that a small number of patients with T2D will be identified through their clinical teams based in hospital outpatient clinics (most people with T2D are managed in primary care) and those attending Allied Health clinics (eg, eye screening and podiatry).

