### Overview of Data Items and Source of Data by Intervention in the Quantitative Study

#### Diabetes My Way

To evaluate the DMW intervention, the University of Manchester will obtain participant data from GP records via DMW, between April 1, 2016, and March 30, 2022. These data will include the following: age, sex, ethnicity, GP postcode (to assess the degree of socioeconomic deprivation) [35], diabetes type and duration, blood pressure, cholesterol, creatinine, estimated glomerular filtration rate (eGFR), smoking and body weight, height, BMI, medication, diabetes clinic attendance in primary care, and hospital visits including emergency visits.

Participant data from DMW or NHS Digital will also include ethnicity (self-provided, sometimes unreliable from primary care due to missing data), user experience or usability, service use (medication, diabetes clinic attendance in primary care, and hospital visits including emergency visits), and website activity.

Data on control participants (not using DMW) will be obtained from NHS Digital, from April 1, 2016, to March 30, 2022, and will include the following: age, sex, ethnicity, GP postcode (to assess socioeconomic deprivation), diabetes type and duration, blood pressure, cholesterol, creatinine, eGFR, smoking and body weight, height, BMI, medication, diabetes clinic attendance in primary care, and hospital visits including emergency visits.

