#### Clinical Data

The clinical data of interest includes age, sex, ethnicity, socioeconomic deprivation, diabetes type, weight, height, BMI, HbA_1c_, blood pressure level, diabetes medication, blood pressure medication, lipid lowering therapy, and service use data (attendance and nonattendance at diabetes clinics and emergency hospital visits) will be obtained from primary care records. Ethnicity will be taken from self-reported data provided at enrollment with DMW (White, South Asian, Black, mixed, or other, if *other* participants will be invited to specify using text). Socioeconomic deprivation will be assessed from the GP postcode to reduce the likelihood of participants being identified.

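### The engagement regression makes no allowance for general practice although deprivation is taken from the GP postcode, so the standard error for deprivation is too small if engagement correlates within practices

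*Protocol article*

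**What the plan says.** The second analysis in the Analysis Overview takes engagement per participant, "as quantified by relevant metrics in the app, eg, visits and time spent". It describes engagement by age, sex, ethnic group and deprivation quintile, then moves to a formal model: "A multiple linear regression model will be used to more formally evaluate the association between the variables listed above (age, sex, ethnicity, and socioeconomic deprivation". General practice does not appear in this model.

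Three data sections give the source of deprivation:
- Data items for Diabetes My Way: "GP postcode (to assess the degree of socioeconomic deprivation".
- Clinical Data: "Socioeconomic deprivation will be assessed from the GP postcode to reduce the likelihood of participants being identified".
- The section on NHS Digital data: "Socioeconomic deprivation level will be assessed from the GP postcode to minimize the risk of patients being identified".

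The matching paragraph of the Analysis Overview also lets general practice stand in for deprivation. The first analysis in the same Overview, the descriptive comparison with people who did not take up the intervention, instead refers to a deprivation quintile based on where the person lives (2019 Index of Multiple Deprivation). The engagement paragraph names no source.

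Clustering is mentioned once, for outcomes measured at two time points: "we will use a simple linear regression model with clustered errors or a paired 2-tailed" t test. The cluster unit is not given.

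**The concern.** A regressor read from the practice postcode takes one value per practice. Its coefficient is therefore estimated from differences between practices, and any other reason why practices differ in engagement adds to its error. A regression that treats participants as independent leaves that component out.

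Such differences are plausible. Under Participants and Recruitment the practice makes the first contact, usually by letter, but "In some cases (according to practice preference), a text message from the practice to the patient or an email sent from the practice" may be used instead. Under Enrollment and Informed Consent, patients need codes obtained through their GP. The Results report 278 people who tried to register but lacked the GP permissions. How the platform fits into primary care pathways is itself an objective. Some of these mechanisms act on enrolment more directly than on later use, so they make a positive within-practice correlation likely but do not prove it.

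The article's conclusions tie the findings to accessibility in more deprived populations and equity of access. This is the only formal model it names for whether engagement varies with deprivation. A gradient that reflected ordinary practice-to-practice variation could misdirect that work.

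**Working it through.** The article states no sample size, alpha, ICC or number of practices for this model, so there is no figure of its own to reproduce.

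**Inputs from the article.** N = 316 enrolled on 10 May 2021 (Results). The 5% level is stated only for the sample size calculation and is borrowed here as two-sided.

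**Assumptions, not in the article.** Participants come from K = 20 to 150 practices. The ICC of engagement is 0 to 0.10. There is no true deprivation effect, and deprivation enters as a linear trend.

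**Formulas**, for a covariate constant within practice and equal practice sizes:
- participants per practice: m = N / K
- design effect: DE = 1 + (m − 1) × ICC
- reported SE / true SE = 1 / √DE
- actual two-sided alpha = 2 × [1 − Φ(1.96 / √DE)]

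**Example.** With K = 20, m = 316 / 20 = 15.8. At ICC 0.05, DE = 1 + 14.8 × 0.05 = 1.74, the SE ratio is 0.76, and alpha = 2 × [1 − Φ(1.96 / 1.319)] = 13.7%.

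| Practices (m) | ICC 0 | ICC 0.01 | ICC 0.05 | ICC 0.10 |
|---|---|---|---|---|
| 20 (15.8) | 5.0% | 6.7% | 13.7% | 21.3% |
| 50 (6.3) | 5.0% | 5.6% | 8.2% | 11.3% |
| 100 (3.2) | 5.0% | 5.2% | 6.3% | 7.6% |
| 150 (2.1) | 5.0% | 5.1% | 5.6% | 6.3% |

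Over this grid the reported SE is between 0.64 and 1.00 of the true one.

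**Uneven practice sizes.** A simulation used 3000 data sets per setting, gamma weights for practice size with a coefficient of variation of 0.8, and two individual-level covariates. The plain regression rejected for deprivation as follows:

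| Practices | ICC 0.01 | ICC 0.05 | ICC 0.10 |
|---|---|---|---|
| 20 | 7.3% | 17.8% | 27.1% |
| 50 | 6.2% | 11.0% | 16.9% |
| 100 | 5.1% | 7.1% | 10.7% |

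The continuous individual-level covariate, which stood in for age and was unrelated to practice, stayed between 4.1% and 5.7% throughout. The excess therefore falls on the practice-level regressor.

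**Ordinary clustered errors.** In the same simulation, practice-clustered errors with the usual scaling factor and t on (number of practices − 1) degrees of freedom rejected in 5.4 to 6.3% with 100 practices, 6.5 to 8.6% with 50, and 9.1 to 10.3% with 20. They are therefore still liberal when practices are few.

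**The case against.** The strongest reply is that a multiple linear regression names the model for the mean and does not rule out clustered standard errors. The analysis plan, which is not shown, may supply them. The authors know the technique, since they name it for another analysis. This stands in part: the article does not say the errors are unclustered. But it specifies this model and its regressors, attaches clustering only elsewhere, and takes deprivation from a practice-level source. The model as named does not suit the exposure as defined.

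The second reply is the residence-based quintile in the first analysis. If that measure is used for engagement, deprivation varies within a practice and the problem shrinks. This also stands, but the data sections list only the GP postcode as the source, and say it was chosen to limit identifiability.

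The third reply is that the size is unknown and could be trivial. This stands in full: with participants thinly spread and a low ICC, the level stays close to 5%.

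A reader might go further and infer that the effective sample for deprivation is nearer the number of practices than the number of patients. The arithmetic does not support that over most of the range. At ICC 0.05 and 10 participants per practice, DE = 1 + 9 × 0.05 = 1.45 and 316 / 1.45 ≈ 218, far nearer 316 than about 32 practices. A reader might also infer that false positives are certainly and heavily inflated. That needs a sizeable ICC and few practices, and the article documents neither.

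**Conclusion.** The point holds conditionally. If deprivation is taken from the GP postcode, and engagement is positively correlated among people in the same practice, the regression as named gives too small a standard error for deprivation and too narrow an interval.

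The direction is clear but the size is not. For 316 participants in equal-sized practices, the actual level of a nominal 5% trend test is about 5 to 6% with 100 or more practices and ICC up to 0.05. At ICC 0.05 it is about 8% with 50 practices and 14% with 20. Uneven practice sizes raise these figures.

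The effect is mainly on the deprivation coefficient. Age and sex should be little affected, and ethnicity only as far as it clusters by practice. This is a secondary, associational analysis, and nothing here touches the primary HbA1c comparison.

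**What to change.** In the engagement paragraph of the Analysis Overview, keep the regressors and add a random intercept for general practice, with Satterthwaite or Kenward-Roger degrees of freedom. Alternatively, use practice-clustered standard errors with a small-sample correction such as CR2. Uncorrected clustered errors, and those with only the usual scaling factor, are not enough if practices are few or uneven. The random-intercept and CR2 versions were not simulated here.

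In the same edit, state which deprivation measure enters the model, and reconcile the GP-postcode wording in the data sections with the residence-based wording in the first analysis.

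No new data are needed, because general practice is already an exact-match variable. The price is a wider interval for deprivation. If the ICC turns out to be near zero, little is lost.

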#### Comparison Group

Within the short time frame available for the study, a randomized controlled trial will not be possible; therefore, the effectiveness of the interventions will be compared with groups of people choosing not to take up the offer of interventions. Data on this comparison group will be sourced from NHS Digital as part of the national GP Data for Planning and Research program. The comparison group will be sourced from patients registered in GM, the other inclusion and exclusion criteria being applied. Controls (not using the intervention) will be matched (up to 10:1) with study participants on age (+2 or −2 years), gender, ethnicity, and general practice. When appropriate, we will increase the number of controls per participant to enable additional matching on baseline levels of outcome measures, such as HbA_1c_ levels. Where there are clinically important differences between participants and controls in relation to other characteristics such as prevalent cardiovascular disease, we will include these variables as covariates regression models.

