### Strengths and Limitations

The main strength of the qualitative study is that we will draw on the experience of a wide range of stakeholders with the aim of capturing the most diverse possible range of perspectives to inform the development of DMW and improve the overall number of patients choosing to engage with the intervention.

One of the limitations of the study is that we will not be recruiting patients who do not understand written English. This may result in a biased patient sample, which is not representative of the diverse population of GM, where an estimated 200 different languages are spoken. However, this may provide a topic for future research. Another limitation is that the study will not formally evaluate the influence of digital exclusion on study outcomes. We anticipate differences in digital literacy and the factors that influence this between participants and controls. However, our matching process, followed by multivariable regression that controls for clinically important covariates not included in the matching process, may help to reduce the influence of digital exclusion. We expect that the results of the qualitative work may provide further insights into the role that digital exclusion might have in the results.

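### Baseline confounders enter the participant-versus-control comparison only where a difference is observed, under three differently worded triggers, instead of through a covariate set fixed in advance

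*Protocol article*

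**What the plan says.** Three places state when a covariate enters, and each is conditional on an observed difference.

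- **Analysis, Overview (general rule):** variables are included "Where there are differences between participants and controls in relation to matched characteristics or other characteristics such as prevalent cardiovascular disease". No size is attached to the difference.
- **Comparison Group:** variables are included "Where there are clinically important differences between participants and controls in relation to other characteristics such as prevalent cardiovascular disease". Here the difference must be important.
- **Analysis, Overview (HbA1c, the main outcome):** change is compared "after adjusting for clinically significant differences in baseline weight, blood pressure, cholesterol, creatinine, cardiovascular disease, and smoking". Six variables are named, but what is adjusted for is a significant difference in them.

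Strengths and Limitations describes the same step without the condition, relying on "our matching process, followed by multivariable regression that controls for clinically important covariates not included in the matching process". There importance belongs to the covariate, not to the imbalance.

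Controls are "groups of people choosing not to take up the offer of interventions". Matching is fixed only on age, sex, ethnicity and general practice. More controls may be drawn "to enable additional matching on baseline levels of outcome measures", such as HbA1c, but only when appropriate. The protocol also expects the groups to differ: "We anticipate differences in digital literacy and the factors that influence this between participants and controls".

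**The concern.** The matched comparison of HbA1c change is the primary outcome for DMW, Oviva and Changing Health. There is no randomisation and the fixed matching is narrow, so regression adjustment carries much of the protection against confounding.

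In such a comparison, the bias left by omitting a covariate is its imbalance times its prognostic strength, and these products add up over covariates. A rule that looks at each imbalance singly uses only one of the two factors and never looks at the sum. People who choose to join may well differ slightly from decliners on several health measures in the same direction. Each difference could be judged too small to matter while the total is not.

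The second cost is discretion. With three wordings and no metric, the covariates in the primary model can be decided after the groups have been compared. This is a rule that the protocol states, not a detail left to an analysis plan. A plan that fixed the covariates outright would have to depart from it.

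**Working it through.** **Inputs from the protocol (Sample Size Calculations; Results; Comparison Group).** SD 15 mmol/mol; target difference 5 mmol/mol; 5% significance level; 86 participants and 430 controls; 316 participants enrolled by May 2021; up to 10 controls per participant, so at most 316 × 10 = 3,160.

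**The plan's own figure.** With 86 versus 430, the normal approximation (two-sided 5%) gives 80.6% power for 5 mmol/mol, so the stated 80% is reproduced for those counts. The standard error is 15 × √(1/86 + 1/430) = 1.77. At 316 versus 3,160 it is 15 × √(1/316 + 1/3,160) = 0.89.

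**Assumptions not in the protocol.** Six independent covariates (the number named for HbA1c); each group difference d = 0.10 to 0.15 SD, all in one direction; each correlation with the outcome r = 0.10 to 0.15; no true effect.

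**Bias before any adjustment.** k × d × r × SD:
- low: 6 × 0.10 × 0.10 × 15 = 0.90 mmol/mol
- high: 6 × 0.15 × 0.15 × 15 = 2.03 mmol/mol

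**Bias and false positives under different entry rules.** Simulation with 1,000 to 2,000 runs per setting. At 1,000 runs a 5% rate has a standard error of √(0.05 × 0.95/1,000) = 0.7 percentage points. SMD is the observed standardised difference. Bias is in mmol/mol.

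| Entry rule | 86 v 430: bias | 86 v 430: false positives | 316 v 3,160: bias | 316 v 3,160: false positives |
|---|---|---|---|---|
| All six always entered | near 0 | about 5% | near 0 | about 5 to 6% |
| SMD at least 0.05 | not tabulated | not tabulated | at most 0.07 | 4.3 to 6.0% |
| SMD at least 0.1 | not tabulated | not tabulated | 0.11 to 0.38 | 5.2 to 7.3% |
| p < 0.05 | 0.59 to 1.01 | 5.9 to 7.5% (r = 0.10) | 0.20 to 0.53 | 5.6 to 8.7% |
| SMD at least 0.2 | 0.45 to 0.80 | about 4 to 7% | 0.81 to 1.39 | 14 to 36% |

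**Weaker prognostic covariates.** With r = 0.03 to 0.05 and d = 0.10, the 0.2 screen leaves a bias of 0.09 to 0.39 and a false-positive rate of 4.5 to 7.9%, against 4.1 to 6.4% with full adjustment.

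**Reading the table.** The result depends heavily on the cutoff, and the cutoff is what the protocol leaves open. Always entering the six variables gives almost no bias from them in every setting.

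**The case against.** Much can be said for the plan. For HbA1c it names six candidate covariates in advance, which limits the choice. The general rule, read literally, admits any difference, and that comes close to full adjustment. The three wordings may be loose versions of one intention. The simulation models an HbA1c level, whereas the plan analyses change from baseline or, with time series data, an interrupted time series that uses pre-intervention trends and controls. Both remove stable level differences, so only covariates related to HbA1c change can bias the result. Optional matching on baseline HbA1c helps too.

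These points limit the size; they do not defend the rule. The HbA1c example, which governs the main outcome, does not say that any difference suffices, and no section commits to entering a covariate whatever the balance.

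Three stronger readings should be resisted.

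- **That about one false positive in three is to be expected.** That needs a 0.2 cutoff, which the protocol does not state, lying just above six independent differences in one direction, and a full 10:1 match that the protocol gives only as an upper limit. It does not describe Oviva or Changing Health, planned at 96 participants each.
- **That the problem grows with the sample.** This holds only for a fixed size cutoff above the true differences. With a p-value screen, the bias falls from 0.59–1.01 to 0.20–0.53 between the two sample sizes.
- **That the six variables belong in every model.** The protocol gives them as an example for HbA1c. Nothing in it supports the list for diabetes distress, the MyCognition primary outcome.

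**Conclusion.** The concern holds as a fault in the entry rule. Three sections make adjustment depend on observed differences, with inconsistent triggers and no metric, while Strengths and Limitations relies on the regression to control for important covariates outright. Confounders already named can therefore stay unadjusted, and the primary model can be chosen after the data are seen.

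The documents do not fix the size. Under the assumptions above, and for cutoffs up to 0.2, residual bias runs from near 0 to about 1.4 mmol/mol, at most 1.4/5 = 28% of the target difference. At the planned 86 versus 430 with a 0.2 screen, the false-positive rate hardly moves (about 4 to 7%), and the bias of 0.45 to 0.80 is under half the standard error of 1.77. At 316 versus 3,160 the rate ranges from about 5% to about 35%, depending on the cutoff. All of this shrinks if the covariates do not predict HbA1c change. The documents do not show that a spurious effect will be reported, only that the rule permits one that could be avoided.

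**What to change.** Replace the conditional wording in Comparison Group and in both places under Analysis, Overview with one rule:

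- The HbA1c participant-versus-control models for DMW, Oviva and Changing Health always include baseline weight, blood pressure, cholesterol, creatinine, cardiovascular disease and smoking, whatever balance is observed.
- Balance between participants and controls is reported descriptively and does not decide what enters.
- Any further adjustment prompted by the data is labelled as sensitivity analysis.
- For every other outcome, including diabetes distress, a covariate set suited to that outcome is fixed in advance by the same rule.

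The cost is wording, a few degrees of freedom, and handling of missing covariate values, for which Missing Data already considers multiple imputation. Cardiovascular disease is not in the listed core data items, although the HbA1c analysis already counts on it, so its source should be confirmed. The change does not remove unmeasured confounding such as digital literacy.
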